## Statistical analysis

Quantitative data will be analyzed using SPSS 21.0 (IBM, New York, NY, USA). The demographic, social, and preclinical characteristics of the subjects in both groups will be described. Differences in these variables between the intervention and control groups will be analyzed using either the Chi-square test or the *T* test, with continuous variables recorded as the mean and standard errors and categorical variables as rates (incidence). For continuous variables, the Shapiro‒Wilk test will be performed to verify that the variables in each group obeyed a normal distribution. For repeated measures, 2-way ANOVA analysis will be conducted. Two independent samples mean comparison *T* tests were used to compare the normally distributed continuous variables between groups. For nonparametric variables, the Kruskal‒Wallis test was used to determine the differences between the groups. Chi-square tests and Fischer exact tests were used to determine differences in categorical variables. Statistical significance was set at *p* < 0.05.

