### Sample size

The sample size is calculated based on the calculation method of a pilot study [21], and the effect size is calculated as follows: *d* = 0.8; *α* = 0.05; Power = 0.8. The minimum sample size per group is 26, and the estimated loss of follow-up/exit rate is 20%. Thus, a maximum of 32 participants will be recruited for each group.

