### Outcomes

#### Clinical knee function evaluation

The estimated follow-up time was 1 day before surgery and 2, 6, 12, and 24 weeks after surgery, and the specific evaluation items included knee ROM (2, 6, 12, 24 weeks after surgery), weight-bearing progress (when fully weight bearing) and knee function and pain scores [23] (Lysholm score, Tegner score, IKDC knee subjective function score, and VAS score). At the final follow-up assessment, return-to-play (RTP) status will be evaluated based on the rehabilitation literature available for meniscus repair. **(**Table 2**)**. [4, 24, 25]

**Table 2 Tab2:** Return-to-play assessment

VAS score = 0	
IKDC score > 90	
No active effusion (Brush test negative)	
The difference in circumference between the quadriceps muscles was less than 1.5 cm	
The knee isokinetic strength test showed a ratio of bilateral quadriceps muscles greater than 90%, bilateral hamstrings greater than 90%, and unilateral hamstrings to quadriceps muscle greater than 66%	
Jump test Limb symmetry index (LSI = jump distance on the affected side/jump distance on the healthy side *100%) was greater than 90%, and the test items included a single-leg long jump test and a single-leg triple jump test	
Y-word balance test: bilateral extension asymmetry within 4 cm; bilateral comprehensive score is greater than 90%	
Lateral step-down test showed no dynamic genu valgus	

The clinical function of patients was assessed and evaluated based on IKDC and VAS score improvement via the criteria of minimal clinically important difference (MCID), patient accepted symptom state (PASS), and significant clinical benefit (SCB) [25].According to the study of Gowd et al. [25], the MCID threshold, which represents the minimal clinically important difference, is defined as an improvement of at least 10.6 points in the IKDC score after treatment or intervention. This threshold signifies that a clinically meaningful change in knee joint function is recognized. The SCB threshold, indicating significant clinical benefit, is set at an IKDC score of 27.3 points or higher after treatment or intervention. This threshold is used to confirm that the treatment has brought about a significant clinical benefit. Lastly, the threshold for patient accepted symptom state (PASS) is established at an IKDC score of 57.9 points or higher. This threshold signifies that patients subjectively consider their symptom state to be acceptable.

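### The planned 2-way ANOVA and unadjusted group tests leave the preoperative score unused as a covariate and, in classical form, drop incomplete patients; a baseline-adjusted mixed model would do better at almost no cost

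*Protocol article*

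**What the plan says.** The Statistical analysis section of the protocol article gives one sentence to the longitudinal scores: "For repeated measures, 2-way ANOVA analysis will be conducted". It does not name the within-patient factor or say whether the preoperative visit is one of the time levels. For group comparisons, two-sample t "tests were used to compare the normally distributed continuous variables between groups"; for variables that are not normal, the Kruskal-Wallis "test was used to determine the differences between the groups". Shapiro-Wilk decides which applies. No covariate is named for any of these analyses.

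Under Clinical knee function evaluation, the assessments are set at "1 day before surgery and 2, 6, 12, and 24 weeks after surgery": one preoperative and four postoperative visits. The same section states: "The clinical function of patients was assessed and evaluated based on IKDC and VAS score improvement". The preoperative score is therefore measured and matters to how the result is read.

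The Sample size section uses d = 0.8, alpha 0.05 and power 0.8, arrives at 26 per group, and adds that "the estimated loss of follow-up/exit rate is 20" per cent, giving 32 recruited per group.

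**The concern.** These are stated methods, so the question is whether they are good choices for these data. There are three weaknesses.

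- **Baseline.** In a small trial, a preoperative measurement of the outcome is usually the most useful covariate available. Neither the ANOVA nor the t-test uses it that way. Because the article judges improvement, a t-test on change from baseline is a natural way to carry out the plan, and that test can lose power rather than gain it.
- **Incomplete follow-up.** A classical repeated-measures ANOVA needs a full row per patient. Someone seen at 2, 6 and 12 weeks but not at 24 contributes nothing.
- **The preoperative visit as a time level.** No treatment effect can exist before surgery, so averaging that visit into the group main effect shrinks it.

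The ANOVA sentence is also loose enough to be run as an ordinary group-by-time ANOVA with each visit an independent row, which would not be valid. Finally, letting a normality test pick the analysis leaves the method unfixed until the outcome data are seen.

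**Working it through.** **Inputs.** From the Sample size section: d = 0.8, alpha 0.05, power 0.80, n = 26 evaluable and 32 recruited per group, 20% loss. From Clinical knee function evaluation: 1 + 4 visits. Assumed, because the article gives no values: a correlation ρ of 0.3, 0.5 or 0.7 between the preoperative and follow-up score and between visits (compound symmetry), and d expressed in follow-up SD units.

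**1. The plan's own figure.** For a two-sided two-sample t-test the noncentrality is d·√(n/2) = 0.8 × √13 = 2.884 on 50 df, which gives power 0.807. So 26 per group is reproduced. For the loss, 26/0.8 = 32.5 and 26 × 1.2 = 31.2; the stated 32 is consistent to within one patient.

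**2. Three ways to compare groups at one visit, n = 26 per group.**
- Follow-up score alone: noncentrality 2.884, whatever ρ is.
- Change score: the SD is multiplied by √(2(1−ρ)), so the noncentrality is 2.884/√(2(1−ρ)), on 50 df.
- Baseline-adjusted (ANCOVA): the SD is multiplied by √(1−ρ²), so the noncentrality is 2.884/√(1−ρ²), on 49 df.

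| ρ (assumed) | Follow-up t-test | Change-score t-test | Baseline-adjusted |
|---|---|---|---|
| 0.3 | 0.81 | 0.67 (2.884/1.183 = 2.438) | 0.84 (2.884/0.954 = 3.024) |
| 0.5 | 0.81 | 0.81 (2.884/1.000 = 2.884) | 0.90 (2.884/0.866 = 3.331) |
| 0.7 | 0.81 | 0.95 (2.884/0.775 = 3.724) | 0.98 (2.884/0.714 = 4.039) |

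The adjusted analysis is best in every row. It would need 24, 20 or 14 per group for 80% power, against 26 unadjusted. A mixed model with the preoperative score as covariate should perform much like this at a given visit when data are complete, and it also uses partial follow-up.

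**3. Incomplete patients.** Complete rows at 20% loss: 64 × 0.8 = 51.2, about 51 patients or 25 to 26 per group. Power of the unadjusted t-test is 0.79 at 25 and 0.81 at 26. The planned loss is therefore already paid for in the sample size. What remains is unused partial data and possible bias if those who leave differ from those who stay.

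**4. Preoperative visit as a time level.** As an illustration, assume the effect builds as 0, 25, 50, 100 and 100% of d = 0.8 over the five visits. The mean effect is 0.8 × 2.75/5 = 0.44. The SD of a patient's mean over m visits is √((1+(m−1)ρ)/m), and the noncentrality is mean effect × √13 divided by that SD.
- Group main effect, five visits: 2.392, 2.048 and 1.820, so power 0.65, 0.52 and 0.43 at ρ = 0.3, 0.5 and 0.7.
- Group main effect, four postoperative visits only (mean effect 0.8 × 2.75/4 = 0.55): 2.877, 2.508 and 2.253, so power 0.81, 0.69 and 0.60.
- Group-by-time test, five visits: power 0.68, 0.84 and 0.98.

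The dilution is real, but it affects the main effect and not the interaction.

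**5. What the ANOVA sentence does to type I error.** 20,000 simulated null trials per setting, 26 per group, five visits:

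| ρ (assumed) | Group effect, visits as independent rows | Group-by-time, independent rows | Group effect, repeated-measures ANOVA |
|---|---|---|---|
| 0.3 | 0.19 | 0.010 | 0.051 |
| 0.5 | 0.26 | 0.001 | 0.051 |
| 0.7 | 0.31 | 0.000 | 0.052 |

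With four visits the independent-rows figures for group are 0.15, 0.21 and 0.27. The approximation 2(1−Φ(1.96/√(1+4ρ))) gives 0.186, 0.258 and 0.315 for five visits, which agrees.

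**The case against.** The strongest reply is that the plan is valid as most readers would take it. The ANOVA sentence opens by referring to repeated measures, so a group-by-time repeated-measures ANOVA is the natural reading, and it holds type I error near 0.05 under compound symmetry. A reader might infer that the plan ignores within-patient correlation and so carries a 19 to 31% false-positive rate. The article does not support that: those figures belong only to the independent-rows reading. What stands is that one added phrase should exclude it.

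A reader might also infer that the preoperative score is thrown away. It is not: IKDC and VAS are judged on improvement, and the preoperative visit may be a level of the ANOVA. What stands is that the score is not used as a covariate.

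On power, an unadjusted randomised comparison is legitimate and reaches the planned 0.81 on follow-up scores. The 0.67 for change scores depends on d being in follow-up SD units, which the article does not state; if d refers to change, that test has 0.81. At ρ = 0.7 the gap between change score and adjustment is small (0.95 against 0.98). The low main-effect power in step 4 is not the whole picture, because the interaction test does better.

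On dropout, the article states no missing-data rule, and one may sit in a fuller document. Losing incomplete patients is a property of the classical method named, not a rule the authors wrote, and the 20% is budgeted. These replies limit the size of the point. None gives a reason to prefer the stated methods.

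**Conclusion.** The point holds as an improvement to a stated method, not as a demonstration that the plan is invalid. The named tests leave the preoperative IKDC and VAS unused as covariates. The classical ANOVA discards partial follow-up and, if it counts the preoperative visit as a time level, weakens the group main effect. At 26 per group, adjustment lifts power from 0.81 to between 0.84 and 0.98 against a follow-up t-test, and from between 0.67 and 0.95 to the same range against a change-score test. The direction of the gain does not depend on which correlation in the range is true; its size does, and the correlations and the SD scale of d are assumptions. The cost of completer analysis is possible bias and wasted data rather than planned power. Type I error is at risk only if the ANOVA is run on independent rows.

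**What to change.** Replace the ANOVA sentence and the group tests for these scores with text along these lines:

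*IKDC and VAS at 2, 6, 12 and 24 weeks will be analysed by a linear mixed model with patient as the repeated unit, an unstructured covariance across visits, and group, visit, group-by-visit and the preoperative score as fixed effects. All randomised patients with at least one postoperative score will be included in their assigned group. The group difference at [one named visit] will be reported with its 95% CI.*

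The deciding visit has to be chosen and written in; the final 24-week visit is one candidate. Keep a rank test as a sensitivity check and remove Shapiro-Wilk as the selector of the test. ANCOVA at the named visit, with a stated approach to missing scores, would also be acceptable.

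The cost is a change of wording, one decision about the visit, and slightly more analysis work. No new data are needed, SPSS is already the planned software, and 26 evaluable and 32 recruited per group can stay as they are.

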## Adverse event management

In this study, inadequate healing of the meniscus may be observed following suturing. After a 6-month postoperative MRI review and clinical evaluation, some patients may require an arthroscopic review to confirm meniscus healing. If the repair of the meniscus is unsuccessful, then partial meniscectomy will be undertaken.

## Data Availability

The datasets used or analyzed during the current study are available from the corresponding author upon reasonable request.
